### Who will take informed consent? {26a}

When patients matching the eligibility criteria are interested in participating in the clinical trial, they are informed by study personnel in detail about the background, aims, treatment protocol, data collection and processing as well as risks and benefits of the trial with the help of a patient information leaflet approved by the Ethics Committee of the Albert-Ludwigs-University, Freiburg, Germany. The patients are encouraged to ask any further questions during this interview. If patients do not have any further questions and wish to participate in the trial, an informed consent form is signed by the participant and the person conducting the informed consent interview prior to digital impression taking.

### Additional consent provisions for collection and use of participant data and biological specimens {26b}

N/a since no biological specimens are collected and since no use of participant data in ancillary studies is planned.

## Interventions

### Explanation for the choice of comparators {6b}

Milled splints are used as comparators as subtractive manufacturing represents the standard CAM fabrication technique for splints. Another option would have been to use splints fabricated conventionally by alginate/silicone impression, cast fabrication, wax-up, and molding from powder-liquid mixtures of PMMA as comparators. It was decided to use milled splints as a comparator since the digital procedure will replace conventional processes due to better time-efficiency and patient comfort [18–20]. In addition, the comparison of two splints fabricated using different CAM processes enables the comparison of splints based on the same digital design and therefore allows differences in splint design/shape to be ruled out as the cause of possible differences in clinical outcome. In contrast, conventionally fabricated and digitally fabricated splints would differ in splint design/shape rendering direct comparison of the effects of the fabrication mode on clinical outcome infeasible.

### Intervention description {11a}

Participants are examined and diagnosed following standard protocols of the DGFDT and the DC/TMD (T0). The BSI, symptom questionnaire of the DC/TMD, the DC/TMD examination form, and the GCPS are used for this purpose. Afterwards, digital impressions of the participants’ upper and lower jaw are taken with an intraoral scanner (Trios 4, 3Shape, Kopenhagen, Denmark), and therapeutic relation, often entitled “centric” relation, is registered as described by Türp [26] with wax sheets at the intended height of the splint (in most cases approx. 2 mm interocclusal space in molar regions). Lateral bite scans are then performed with the intraoral scanner and the adapted wax sheet in situ. Based on this data set, the Michigan-type stabilization splints are designed with the software SplintStudio (3Shape). Then, based on this design, one occlusal splint is 3D printed from Primeprint splint (Dentsply Sirona, Bensheim, Germany; the material is marketed by Dentsply Sirona under the name Primeprint Splint, but is manufactured by DETAX, Ettlingen, Germany as Freeprint Splint 2.0, i.e., Primeprint splint and Freeprint Splint 2.0 are the same materials and both have the UDI DI EDET0465W). The 3D printing process is carried out using a Primeprint printer (Dentsply Sirona). Subtractively manufactured splints are milled from Ceramill A-Splint blanks (Amann Girrbach, Pforzheim, Germany) with an inLab MC X5 (Dentsply Sirona, Bensheim, Germany). The materials are processed as specified by the manufacturers. Participants are instructed to wear the splints at night.

Starting with the incorporation of the first splint, the trial is carried out according to the following protocol:

Incorporation of the 1^st^ splint (T1): scan of the splint as delivered from the laboratory with the intraoral scanner and—if necessary—also after adjustment, completion of the Oral Health Impact Profile (OHIP-G14, German version from 2005) by all participants of both cohorts, completion of the GCPS by participants of the TMD cohort, examination of the TMD patients according to the DC/TMD standardControl 2 weeks after incorporation of 1^st^ splint (T2): if necessary, adjustment and scan of the splint, completion of the OHIP-G14 and GCPS and examination of TMD patients as described above, rating of wear comfort and retention of the stabilization splints on a VAS scale of 1–10 by participants of both cohortsControl 3 months (11–13 weeks) after incorporation of the 1^st^ splint (T3): scan of the splint and opposing dentition with the intraoral scanner, completion of the OHIP-G14 and GCPS, examination of TMD patients and rating of wear comfort and retention as described for T2, scan of the 2^nd^ splint as delivered from the laboratory and—if necessary—also after adjustment, incorporation of the 2^nd^ splint.Control 2 weeks after incorporation of 2^nd^ splint (T4): see T2Control 3 months (11–13 weeks) after incorporation of the 2^nd^ splint (T5): see T3. Additionally, the participant is asked to name his or her favorite splint (1^st^ or 2^nd^)

A wash-out period between the two splints was not included, as this may lead to aggravation of symptoms and therefore bears the risk that patients may switch to alternative treatment options such as commercially available splints to alleviate symptoms during the wash-out period, rendering trial conditions less controlled.

### Criteria for discontinuing or modifying allocated interventions {11b}

Criteria for discontinuing or modifying allocated interventions for a given trial participant are the occurrence of exclusion criteria for the respective cohort or the withdrawal of consent. Interventions may also be discontinued if a participant unexpectedly experiences a worsening of symptoms that the participant considers intolerable.

### Strategies to improve adherence to interventions {11c}

From the strategies to improve adherence in clinical research proposed by Robiner [27] and Matsui [28], the following aspects are considered in this trial: the study personnel spends sufficient time during the first examination to assess the participants’ potential adherence. The protocol, the benefits for (future) patients, and the importance of adherence are explained in detail to participants to help them understand the objectives of the trial and the importance of their adherence. Participants are explicitly informed about when and how to wear the splint. The appointments are scheduled at convenient times and the splints are offered free of charge to compensate for the time required to participate in the trial. Adherence is monitored by self-report of the participants. In general, participants can be assumed as intrinsically motivated to wear the splints, since this will reduce teeth abrasion and/or pain.

### Relevant concomitant care permitted or prohibited during the trial {11d}

During participation in the trial, participants should not undergo concomitant treatments or interventions like botulinum toxin injections into masticatory muscles, pain therapy with prescription painkillers, muscle relaxants, or physiotherapy. If any of these measures are necessary for medical reasons, further participation in the trial will be discussed on an individual basis. Short-term use of over-the-counter painkillers is permitted as well as application of heat/cold, self-massage, and continuation of physiotherapy exercises already learnt prior to the trial.

### Provisions for post-trial care {30}

Only established treatment modalities with a very low risk for adverse events are applied and participants can remove the splints themselves when they feel uncomfortable with them. Harm induced by trial participation, therefore, appears improbable which is the reason why no compensations for harm suffered from trial participation are deemed necessary. Participants can keep both splints after trial participation and are invited to regular controls at our department.

### Outcomes {12}

#### Primary outcomes

As the primary outcome, the OHRQoL of the participants is assessed using the OHIP-G14 questionnaire on the day of incorporation and after 2 weeks and 3 months after incorporation of each splint. Depending on the answer options ticked by the participants, this questionnaire results in scores between 0 and 56. For each participant and splint, the difference from the baseline (incorporation of splint) is evaluated at 2 weeks and 3 months post insertion.

Additionally, participant satisfaction with the stabilization splints is investigated by asking the questions “How comfortable was wearing the splint for you on a scale from 1 (very uncomfortable) to 10 (very comfortable)?” and “How stable did the splint rest in your mouth at a scale from 1 (very unstable) to 10 (very stable)?”. These questions are asked at the 2 weeks and 3 months controls and are analyzed for differences in relation to the manufacturing method.

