### Sample size {14}

The sample size was calculated based on results reported for the OHIP-G14. According to the results of Alajbeg et al. [29], an OHIP-G14 score of 25.29 (SD 12.38) can be assumed for TMD patients. If the non-inferiority margin is set at 5 and a standard deviation of the differences of 10 is assumed, 38 participants are required for the trial with a two-sided paired t-test and a power of 90% on a 5% significance level. As both cohorts can be analyzed together for the primary outcome parameter OHIP-G14, the target number of cases is set at 20 participants per cohort, resulting in 40 participants in total.

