## Statistical methods

### Statistical methods for primary and secondary outcomes {20a}

Absolute and relative frequencies are calculated for binary or categorical variables. For continuous data, the median, mean and standard deviation are specified. In addition, 95% confidence intervals are calculated. The calculations are performed per group (milled and 3D printed) and per cohort (bruxism and TMD). Cross-over effects are examined in all analyses. For the primary outcome parameter OHIP-G14, the group differences are estimated and tested using a linear regression model with corresponding two-sided 95% confidence intervals. The model will include the difference in OHIP-G14 values (milled vs. 3D printed) as a dependent variable and the sequence of the splints and the cohort (bruxism and TMD) as independent variables.

The one-sided test for non-inferiority of 3D printed versus milled splints at the 2.5% significance level is based on the two-sided 95% confidence interval of the linear regression model. The null hypothesis is rejected if the lower limit of the confidence interval for the difference (conventionally milled vs. 3D printed) is above − 5. The same applies to secondary outcomes, namely volume loss of the splint/opposing dentition, pain reduction, jaw mobility, and splint fracture rates.

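### The primary OHIP-G14 change score takes the first splint's 3-month result as the second splint's baseline, and the plan does not say whether the model, margin and SD refer to these changes or to visit scores

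*Protocol article*

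**What the plan says.** All places are in the protocol article.

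- **Primary outcomes (Outcomes {12}).** The OHIP-G14 variable is a change per splint: "For each participant and splint, the difference from the baseline (incorporation of splint) is evaluated at 2 weeks and 3 months post insertion". No other OHIP-G14 variable is defined for evaluation.
- **Intervention description {11a}.** The first splint is inserted at T1 and reviewed at T2 and T3. The second is inserted at T3 and reviewed at T4 and T5. At T3 the questionnaires are listed once: "completion of the OHIP-G14 and GCPS, examination of TMD patients and rating of wear comfort and retention as described for T2". On the gap between periods: "A wash-out period between the two splints was not included, as this may lead to aggravation of symptoms".
- **Statistical methods {20a}.** "The model will include the difference in OHIP-G14 values (milled vs. 3D printed) as a dependent variable", with "the sequence of the splints and the cohort (bruxism and TMD) as independent variables". Non-inferiority is concluded if the lower 95% confidence limit for milled versus printed lies above -5. On carry-over the section says only: "Cross-over effects are examined in all analyses".
- **Sample size {14}.** "If the non-inferiority margin is set at 5 and a standard deviation of the differences of 10 is assumed". The result is 38 participants for 90% power with a two-sided paired t-test at 5%, rounded up to 40.
- **Secondary outcomes.** GCPS scores and painful points are likewise compared with the incorporation day. Jaw mobility is measured at the same visits, but no change score is defined for it.

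**The concern.** Each splint appears to have its own baseline, but only the first one does. T1 precedes wear of either trial splint. T3 follows three months on the competing splint. The first splint is thus measured against a state without a trial splint, and the second against a state already treated by its comparator, so the treatment effect enters the second baseline.

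A non-inferiority test needs the variable, the margin and the SD to describe one quantity. Here the outcome section defines changes, the model section speaks of values, and the sample-size section gives an SD of differences without saying which difference. If the changes are carried into the model, the -5 limit is applied to something other than the milled-minus-printed difference, and the contrast is noisier than a simple paired difference. The sequence term absorbs an average period effect. It alters neither the scale nor the variance.

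**Working it through.** **Inputs.** Margin 5, SD of differences 10, between-patient SD 12.38, N = 40 (Sample size {14}); one-sided 2.5% (Statistical methods {20a}). Contrasts are milled minus printed. The direction of the -5 rule implies that a higher score is worse, so a printed deficit is negative.

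**1. The plan's own figure.** With true difference 0, n = (10 × (1.960 + 1.282) / 5)², which gives 43 by the normal approximation and 44 by the noncentral t. The stated 38 is the noncentral t result for 85% power. That is a separate matter. What is needed here is power at N = 40 with SD 10, which is 86.8% (37 df).

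**2. What the difference of changes estimates at 3 months.** Let m and p be the milled and printed effects, d = m - p, and μ1, μ3, μ5 the visit means. Assume no carry-over.

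- Milled first: (T3 - T1) - (T5 - T3) = 2·T3 - T1 - T5, with expectation (2μ3 - μ1 - μ5) + 2m - p.
- Printed first: (T5 - T3) - (T3 - T1) = T5 - 2·T3 + T1, with expectation -(2μ3 - μ1 - μ5) + m - 2p.
- Average over sequences: (3m - 3p)/2 = 1.5d. The visit means cancel.

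The -5 limit then corresponds to d = -5/1.5 = -3.33. The difference of scores, T3 against T5, averages to d. A simulation (N = 40, 3,000 runs) at d = -2 gave -3.00 for changes and -2.00 for scores.

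The 2-week changes give the 2-week difference plus half the 3-month difference, again 1.5d if the two are equal.

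**3. Variance.** If SD 10 is that of the score difference, 2s²(1 - ρ) = 100. With s = 12.38, ρ = 1 - 100/(2 × 153.26) = 0.674.

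- Equal correlations: Var(T5 - 2·T3 + T1) = 6s²(1 - ρ) = 300, SD 17.3, ratio 3. This ratio needs neither 12.38 nor ρ.
- First-order decay: s²(6 - 8ρ + 2ρ²) = 232.6, SD 15.3, ratio 3 - ρ = 2.33.
- Other patterns (T1–T3, T3–T5, T1–T5): 0.4, 0.7, 0.4 gives a ratio of 4.0; 0.8, 0.5, 0.5 gives 1.8.

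**4. Power with equal splints** (noncentral t, N = 40, 37 df, limit -5):

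| Contrast | SD | Power | N for 90% |
|---|---|---|---|
| Scores, T3 vs T5 | 10 | 86.8% | 44 |
| Changes, first-order decay | 15.3 | 52.4% | 100 |
| Changes, equal correlations | 17.3 | 42.8% | 129 |

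**5. Carry-over.** Suppose a fraction L of the first splint's effect persists at T5. The factor becomes 1.5 - 0.5L for changes and 1 - 0.5L for scores. At L = 1 the change contrast is undistorted and the score contrast is halved.

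**6. False non-inferiority at a true printed deficit of 5.** Changes, no carry-over, SD 17.3: 0.2%. Scores, SD 10: 2.5% at L = 0, 5.8% at L = 0.25, 11.7% at L = 0.5, 33.7% at L = 1.

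**The case against.** The strongest objection is that the plan never says the changes are what is tested. Values in the model section can mean visit scores, and a paired t-test with an SD of differences fits the simple T3-versus-T5 difference. On that reading the test is already the right one and the outcome section describes a further evaluation. This stands to the extent that every figure above is conditional. It does not remove the point, because the change from incorporation is the only OHIP-G14 variable the article defines, so the sections still need reconciling.

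Three stronger readings are tempting, and the document does not support them.

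- A reader might infer that the plan biases the trial towards a false non-inferiority claim. It does not: without carry-over the 1.5 factor is conservative when printed is worse (0.2% against a nominal 2.5%) and has no effect when the splints are equal. The costs are lost power and an exaggerated printed advantage, if there is one.
- A reader might take 43% as the trial's power, or threefold as the largest variance inflation. Neither is established. The loss presupposes that SD 10 belongs to the score difference. If it was meant for the change contrast, there is no loss from this source. Threefold is not a ceiling either, as the ratio of 4.0 shows. Moreover, 12.38 is given for TMD patients only, while half the sample has bruxism; this affects the decay scenario but not the equal-correlation one.
- A reader might extend the defect to jaw mobility. No change score is defined there, so that does not follow.

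The objection that the remedy has its own hazard also stands. In a design without wash-out, carry-over cannot be dismissed, and it dilutes the score contrast in the anti-conservative direction.

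**Conclusion.** The concern holds in conditional form. It is certain that the defined primary change score uses the first splint's 3-month outcome as the second splint's baseline, and that the outcome, model and sample-size sections do not establish one common quantity.

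If the difference of changes is tested and there is no carry-over, the estimate is 1.5 times the true difference and the margin of 5 acts as one of about 3.3 points. If in addition SD 10 refers to the score difference, the variance is about 2.3 times (first-order decay) to 3 times (equal correlations) as large, and larger still if T1 correlates weakly with later scores. Power at N = 40 then falls from about 87% to about 52% or 43%. These figures further assume equal variances across visits. The point should be settled before analysis because it determines what the primary test means.

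**What to change.** In Primary outcomes and in Statistical methods {20a}:

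1. Define the primary variable as the within-participant milled-minus-printed difference of OHIP-G14 scores at the same post-insertion visit of each period: T3 versus T5 for the 3-month comparison, T2 versus T4 for the 2-week one.
2. Keep sequence and cohort in the model, effect-coded so that the intercept is the treatment difference. Use T1 at most as a covariate, and never T3 as a baseline. Changes from T1 may be reported descriptively.
3. State, also in Sample size {14}, that the margin of 5 and the SD of 10 apply to this difference.
4. State the downside: the contrast assumes negligible carry-over at T5. If a fraction L of the first splint's effect persists, it shrinks by the factor 1 - 0.5L, which is anti-conservative for non-inferiority.
5. Apply the same rule to the GCPS and painful-point comparisons in Secondary outcomes, and to jaw mobility only if a change score is used.

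The cost is wording, plus an amendment if the full protocol carries the same text. No new visits or data are needed. Per-splint changes from incorporation cease to be the primary variable.

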
### Objectives {7}

Therefore, the objective of this clinical trial is to analyze whether the clinical outcome of 3D printed stabilization splints is inferior compared to milled stabilization splints in terms of patients´ OHRQoL and satisfaction with the splints, therapeutic efficacy, and technical outcome. These parameters will be investigated in both—a cohort comprising participants with bruxism and a cohort with participants suffering from pain-related TMD—over a period of 6 months. The null hypothesis states that novel 3D printed stabilization splints for use in bruxism or TMJ and/or jaw muscle pain are not inferior to milled stabilization splints with regard to the aforementioned parameters.

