For the diagnosis of TMD, the DC/TMD, primarily established as RDC/TMD in 1992 and updated in 2014, can be regarded as the standard assessment and diagnostic tool [30]. For this reason, participants are examined and diagnosed following the guidelines of the DC/TMD in the present trial. Only pain-related TMDs are included in the trial as these conditions—but not pain-free intra-articular TMD—can be effectively managed by stabilization splints. These diagnoses are also used to discern the bruxism cohort, in which such a diagnosis led to exclusion. As an additional tool to assess trial eligibility, the GCPS is applied in the TMD cohort as a short, reliable, and valid instrument [38] for which a correlation with splint treatment effects was established [39]. Patients with GCPS grade III and IV are excluded since these scores point to high pain and moderate to severe disability that in most cases cannot be sufficiently alleviated by splint treatment and instead require multimodal pain therapy [39].

The bruxism and TMD cohort are then investigated for differences in OHRQoL and participant satisfaction with the splints in relation to their fabrication mode. OHRQoL was chosen as the primary outcome parameter, as OHRQoL with the splints determines participant compliance and thus the use of the splint, which consequently has an impact on the therapeutic efficacy and the technical outcome of the splint. The assessment of OHRQoL, therefore, forms the base for the future selection of treatment options enabling a maximum of treatment comfort and benefit for the patients [40]. For assessment of OHRQoL, the OHIP-G14 is used, which is an established questionnaire focusing on the evaluation of oral function, orofacial pain, orofacial appearance, and psychological impact [41–44]. To further integrate questions that specifically focus on participant satisfaction with the splints, participants are asked to rate wear comfort and retention of the splints on a Visual Analog Scale (VAS). Therapeutic efficacy and technical outcome are evaluated since these parameters determine clinical applicability as well as the service life of the splints and are therefore—in conjunction with OHRQoL—important measurements for the cost and benefit ratio. Especially for the GCPS, it was shown that it allows monitoring of even small changes in TMD symptoms [20] turning it into a sensitive instrument to validate therapeutic efficacy.

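### Satisfaction is part of the non-inferiority question, but the plan gives the comfort and stability ratings no margin and no rule by which they could be called not inferior

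*Protocol article*

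**What the plan says.** - **Objective.** Objectives {7} asks whether printed splints are "inferior compared to milled stabilization splints in terms of patients´ OHRQoL and satisfaction with the splints, therapeutic efficacy, and technical outcome". The null hypothesis there is that printed splints "are not inferior to milled stabilization splints with regard to the aforementioned parameters", which includes satisfaction.
- **Outcome.** Under the Primary outcomes heading, OHIP-G14 is introduced as the primary outcome. Then: "Additionally, participant satisfaction with the stabilization splints is investigated by asking the questions". Comfort and stability are each rated from 1 to 10, with 10 the best. On analysis: "These questions are asked at the 2 weeks and 3 months controls and are analyzed for differences in relation to the manufacturing method".
- **Decision rule.** Statistical methods {20a} judges OHIP-G14 by the two-sided 95% confidence interval from a linear model with sequence and cohort as covariates. The lower limit for milled versus printed must be above −5. The section then adds: "The same applies to secondary outcomes, namely volume loss of the splint/opposing dentition, pain reduction, jaw mobility, and splint fracture rates". Comfort and stability are not on that list.
- **Pooling.** Sample size {14} states pooling for one outcome: "As both cohorts can be analyzed together for the primary outcome parameter OHIP-G14". No margin, SD or sample size is given for the ratings.

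**The concern.** An objective framed as inferiority needs an inferential rule that can answer it. OHIP-G14 has one: an interval compared with a margin. The ratings are in the same objective, but the article gives them only a comparison for differences. A comparison without a margin cannot establish non-inferiority. The noisier the ratings, or the fewer the complete pairs, the more likely it is that no difference will be found.

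At stake is a statement that printed splints are no worse in comfort or stability. These are the outcomes that ask most directly about the splint itself, and such a statement could rest on imprecision alone.

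**Working it through.** **1. Can the existing rule be borrowed?** The limit of −5 applies to OHIP-G14, which runs from 0 to 56. The ratings run from 1 to 10, a span of 10 − 1 = 9 points, so 5 points would be more than half the scale. The direction also fails. Reading the contrast as milled minus printed, a lower limit above −5 bounds how much higher the printed score may be. That is the right side for OHIP-G14 if higher scores mean more impairment. For ratings where higher is better, it would bound the advantage of the printed splint and not its deficit.

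**2. The plan's own figure.** There is none for satisfaction. The only sample size, 38, is for OHIP-G14 (margin 5, SD of differences 10, two-sided 5%, 90% power). A paired t-test with these inputs needs 44 and has 85.1% power at 38. That discrepancy is a separate matter, and nothing below depends on it.

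**3. How often would a real deficit go undetected?** The article does not name a test for the ratings, so a two-sided 5% paired t-test is assumed. With d the true deficit in SDs of the paired difference:

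miss rate = P(T ≤ t₀.₉₇₅,ₙ₋₁), where T is noncentral t with n − 1 degrees of freedom and noncentrality d√n.

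For d = 0.5:
- n = 40: noncentrality 0.5 × √40 = 3.162, critical value 2.023, miss rate **13%**.
- n = 20: noncentrality 0.5 × √20 = 2.236, critical value 2.093, miss rate **44%**.

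If the deficit is 0.5 SD of the rating itself, then d = 0.5/√(2(1 − ρ)), with ρ the within-person correlation. The article does not give ρ, so a range is shown:

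| ρ | d | Miss rate, 40 pairs | Miss rate, 20 pairs |
|---|---|---|---|
| 0 | 0.354 | 41% | 68% |
| 0.3 | 0.423 | 26% | 57% |
| 0.6 | 0.559 | 7% | 34% |

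In scale points, a true 1-point deficit with an assumed SD of differences of 2, 2.5 or 3 is missed 13%, 31% or 46% of the time with 40 pairs, and 44%, 60% or 71% with 20.

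**4. What would a margin rule achieve?** Take an illustrative margin of 1 point, a true difference of 0, one-sided 2.5% and 40 pairs:

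| Assumed SD of differences | Power, 40 pairs | Pairs for 90% power |
|---|---|---|
| 1.5 | 98% | 26 |
| 2 | 87% | 44 |
| 2.5 | 69% | 68 |
| 3 | 54% | 97 |

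**The case against.** - **Looking for differences may be only a general phrase.** The Discussion uses similar wording for quality of life and satisfaction together, and quality of life is nevertheless judged against a margin. This stands: the wording does not prove that a significance test of difference is intended. It does not supply a rule either, because the list under the margin rule is explicit and omits the ratings.
- **A reader might infer that a non-significant result will be reported as non-inferiority.** The article never says so. The null hypothesis in the Objectives points that way, since failing to reject it leaves not inferior standing. But the same wording covers OHIP-G14, for which the Statistical methods reverse it: there, rejecting the null establishes non-inferiority. The inference is therefore a risk left open and not a stated plan.
- **A reader might treat satisfaction as a co-primary outcome.** The ratings sit under that heading, but the Discussion says "OHRQoL was chosen as the primary outcome parameter", and the Sample size and Statistical methods sections also name OHIP-G14 as the primary parameter. The point rests on the Objectives and not on the label.
- **A reader might take 20 pairs as the planned sample.** The per-cohort sentence follows the descriptive statistics and also covers OHIP-G14, which is pooled. An analysis of 40 pairs is not excluded.
- **The detail may be in the full protocol or analysis plan.** A missing margin alone could be left there. Here, however, the article sets an inferiority objective, describes the analysis of the ratings, and limits the margin rule to other outcomes. Those statements do not fit together. The article also provides for 95% intervals on continuous data, which helps, but an interval without a margin still gives no decision.
- **Large deficits would be seen.** This is true: at 0.8 SD of the differences the miss rate is 8% with 20 pairs and 0.1% with 40. The concern is with moderate deficits.

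**Conclusion.** The point holds in this form: the article includes satisfaction in its inferiority question but provides no valid route to a not-inferior conclusion on it. Apart from failure to find a difference, nothing in the text could support one.

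The size depends on pooling and on variability that the article does not give. For a deficit of 0.5 SD of the paired differences, the miss rate is 13% pooled and 44% per cohort. For 0.5 SD of the rating, with correlation from 0 to 0.6, it is 41% to 7% pooled and 68% to 34% per cohort. All of these figures assume a two-sided 5% paired t-test and complete pairs. The OHIP-G14 analysis is not affected. The change is worth making because it costs little and decides whether a satisfaction claim can be defended.

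**What to change.** Before unblinding, add to the Statistical methods:

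1. Comfort and stability at 3 months are analysed in the pooled OHIP-G14 model, with sequence and cohort as covariates. The estimate is printed minus milled (higher is better), with its two-sided 95% confidence interval.
2. Non-inferiority is claimed for a rating only if the lower limit is above a margin on the 1–10 scale, fixed in advance and justified. The 1-point margin used above is an illustration and has no basis in the article. At an SD of differences of 2.5 or more, 40 pairs would give it 69% power or less.
3. If no margin can be justified, the interval is reported as supportive, with a statement that a non-significant difference is not evidence of non-inferiority. Satisfaction is then removed from the non-inferiority claim in the Objectives.

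The cost is wording only, with no extra data or participants. The downside is that the satisfaction claim becomes harder to make, or is withdrawn.
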